**Methods:**

The project “Underlying mechanisms in the relationship between stress and alcohol consumption in regular and risky drinkers (MESA)” is a randomized controlled study that started in December 2018 and is conducted in a laboratory setting, which aims to identify moderators and mediators of the relationship between acute stress and alcohol consumption among regular and risky drinkers. Regular and risky drinkers are randomly assigned to a stress induction or a control condition. Several processes that may mediate (emotional distress, endocrine and autonomic stress reactivity, impulsivity, inhibitory control, motivational sensitization) or moderate (trait impulsivity, childhood maltreatment, basal HPA-axis activity) the relation between stress and alcohol consumption are investigated. As primary dependent variable, the motivation to consume alcohol following psychosocial stress is measured.

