### Aims and hypotheses

The present and ongoing study aims to fill this research gap by conducting an experimental laboratory design to investigate the underlying mechanisms of the association between stress and alcohol consumption (MESA) in the at-risk population of young men. Since these mechanisms are expected to differ depending on the stage of alcohol use, they are examined in regular and risky drinkers. Therefore, several processes that could mediate the relation between stress and alcohol consumption at different stages of alcohol use progression are assessed.

The research questions are as follows:Does acute stress increase alcohol consumption in a laboratory setting?What are the mediators of the association between acute stress and alcohol use?What are the moderators of the association between acute stress and alcohol use?Are effects of acute stress on alcohol use as well as moderators and mediators of this association different in risky drinkers compared to regular drinkers?

The following a priori hypothesis were formulated:Acute stress increases alcohol consumption in a laboratory setting.This effect is stronger in risky compared to regular drinkers.Emotional distress, endocrine and autonomic stress reactivity as well as impulsivity account for most of the effect of stress on alcohol use in regular drinkers (mediation).Emotional distress, endocrine and autonomic stress reactivity, impulsivity, attentional bias and craving account for most of the effect of stress on alcohol use in risky drinkers (mediation).A history of childhood maltreatment, basal HPA-axis activity and impulsivity are related to a stronger effect of acute stress on alcohol consumption in regular and risky drinkers (moderation).

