### Assessment

#### Person-related measures

Participants complete a comprehensive baseline assessment (questionnaire package) including the measures of the proposed moderators (childhood maltreatment, trait impulsivity), mediators (attentional bias to alcohol related stimuli, inhibitory control and impulsivity, and stress reactivity during the acute stressor), and variables that might affect the associations of interest (usual alcohol consumption, drinking motives, perceived stress, trait anxiety, difficulties in emotion regulation, psychological flexibility) (Table 1).

**Table 1 Tab1:** Variables and assessment instruments

Variable	Assessment	References
*Exclusion criteria*	Screening questions of the Structural Clinical Interview for DSM-IV	[59, 60]
Psychotic symptoms		
Suicidality		
Probable alcohol use disorder		
*Stratification variable*		
Usual alcohol consumption	Self-administered timeline followback	[58, 61]
*Moderators*		
Childhood adversities	Childhood trauma questionnaire (CTQ)	[62, 63]
Trait impulsivity	Impulsive Behavior Scale (UPPS)	[61, 64]
Cumulative cortisol secretion	Hair cortisol concentration	[56, 59]
*Mediators*		
Endocrine stress reactivity	Salvia cortisol concentration	[60, 65]
Autonomic stress reactivity	Salvia alpha amylase concentration	[63, 66]
Inhibitory control	Go-no-go task	[64, 67]
Attentional bias	Dotprobe task	[41]
Impulsivity	Delay discounting task	[68, 69, 70]
*Confounding variables*		
Current stress load	Perceived stress scale (PSS)	[67, 71]
Psychological flexibility	Acceptance and Action Questionnaire (AAQ-II)	[68, 72]
Drinking motives	Drinking Motive Questionnaire- revised (DMQ-R)	[69, 73]
Craving	Alcohol Craving Questionnaire revised (ACQ-R)	[71, 74]
Emotion regulation	Difficulties in Emotion Regulation Scale (DERS)	[75, 76]
Trait anxiety	State-Trait-Anxiety-Inventory (STAI)	[73, 77]
Positive and negative affect	State-Trait-Anxiety-Inventory (STAI)	[73, 77]
General condition	Multidimensional Mood State Questionnaire. (MBDF)	[74, 78]
Drug use	Drug screening	
Attentional control	Attentional control scale (ACS)	[75, 79]
Negative thinking	Perseverative thinking questionnaire (PTQ)	[77, 80]
Sleep quality	Pittsburgh sleep quality index (PTQI)	[78, 81]
Uncertainty intolerance	Uncertainty intolerance scale (UIS)	[79, 82]
Coping strategies	Brief Cope	[80, 83]
Depression	Becks Depression Inventory (BDI)	[81, 84]
Self-control	Brief self-control scale (BSCS)	[82, 85]

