### Statistical analyses

Main effects of stress exposure (stress vs control group) on alcohol consumption (amount of alcoholic beverage consumed) will be determined using linear regressions adjusting for the amount of non-alcoholic beverages consumed (which reduces unspecific variance in outcome). However, in case of considerable by chance differences in baseline characteristics between the two groups despite randomization, these characteristics will be included in the regression model if they are associated with alcohol consumption. To address potential biases related to missing data, we will conduct sensitivity analyses using multiple imputation.

Moderation analyses: Moderators are defined causally [50]. Linear regressions with interaction terms will be applied to test whether stress effects on alcohol consumption are moderated by childhood maltreatment, hair cortisol concentration and trait impulsivity (with main effects terms and interaction term, e.g. group × childhood maltreatment). Significant interactions indicate that a respective factor (moderator) predicts different effects of stress on alcohol assumptions. To approach causal conclusions, we will fit these models again while adjusting for shared factors of moderators and outcomes (e.g. previous stressful events, previous alcohol use) [50].

Mediation analyses: Mediators are also defined causally according to the counterfactual definition of Robins and Greenland [115] that is implemented in the ‘paramed’ package in Stata. This module allows dividing the estimated total stress effect (stress vs. control group) on alcohol consumption into a direct effect and an indirect effect mediated through stress reactivity (saliva cortisol, alpha amylase, self-reported stress), impulsivity (delay discounting), inhibitory control, and motivational sensitization (attentional bias). Mediation analyses will be adjusted for putative sociodemographic (e.g. age) and other shared factors of a potential mediator and outcome (e.g. time of day, preference of beer) as well as for the mentioned factors for moderation. The alpha level will be specified at two-sided 0.05. If necessary, the analyses will be repeated with robust standard errors (via the sandwich estimator) and robust linear regressions [116]].

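### Craving is a hypothesised mediator in risky drinkers, but Table 1 classes it as a confounder and the mediation analysis leaves it out, so that hypothesis cannot be fully tested

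*Protocol article*

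**What the plan says.** The hypotheses are unnumbered in the article. H3 and H4 below mean the third and fourth in order.

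- **H3, regular drinkers (Aims and hypotheses):** "Emotional distress, endocrine and autonomic stress reactivity as well as impulsivity account for most of the effect of stress on alcohol use in regular drinkers".
- **H4, risky drinkers (same section):** "Emotional distress, endocrine and autonomic stress reactivity, impulsivity, attentional bias and craving account for most of the effect of stress on alcohol use in risky" (quotation cut before its final noun).
- **Abstract, Methods:** the possible mediators are "emotional distress, endocrine and autonomic stress reactivity, impulsivity, inhibitory control, motivational sensitization". Craving is not named separately.
- **Table 1, Mediators block:** salivary cortisol, salivary alpha-amylase, the go/no-go task, the dot-probe task and delay discounting.
- **Table 1, block headed "Confounding variables":** this holds craving, by the "Alcohol Craving Questionnaire revised (ACQ-R"), and general condition, by the "Multidimensional Mood State Questionnaire. (MBDF"). Positive and negative affect, by the STAI, is in the same block.
- **Statistical analyses, mediation paragraph:** the indirect effect runs through stress reactivity (cortisol, alpha-amylase and self-reported stress) and through "impulsivity (delay discounting), inhibitory control, and motivational sensitization (attentional bias"). These models are adjusted for sociodemographic variables, for other factors common to mediator and outcome, and for the factors named for the moderation models.

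**The concern.** The article gives craving three incompatible roles: a mediator in H4, a confounder in Table 1, and no role in the mediation analysis. The Background (Mediators and moderators) also places craving downstream, as something that heightened attention to alcohol cues increases. That fits H4 and does not fit the confounder label.

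H4 adds exactly two mediators to H3, attentional bias and craving. The fourth research question asks whether the mediators differ between risky and regular drinkers, so these two carry the predicted difference. If the analysis is run as written, half of that difference is never examined. If the conflict stays open, the role of craving can be settled after the data have been seen.

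**Working it through.** There is no figure to recompute. The check is a comparison of three lists, taking the six mediators of H4 one at a time.

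| H4 mediator | Also in H3? | Block in Table 1 | In the mediation analysis? |
|---|---|---|---|
| Emotional distress | Yes | No instrument in the Mediators block; affect and mood state are under confounders | Only as self-reported stress |
| Endocrine reactivity | Yes | Mediators (salivary cortisol) | Yes |
| Autonomic reactivity | Yes | Mediators (alpha-amylase) | Yes |
| Impulsivity | Yes | Mediators (delay discounting) | Yes |
| Attentional bias | No | Mediators (dot-probe) | Yes |
| Craving | No | Confounders (ACQ-R) | No |

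**Count.** Five of six have a counterpart in the analysis and one has none. H4 minus H3 leaves 6 − 4 = 2 mediators, of which one is analysed.

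**Can craving be read into another entry?** The nearest is motivational sensitization. The mediation paragraph puts a single measure in the parenthesis after that construct, attentional bias, so craving is not covered there.

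**What this does to H4.** H4 claims that a set of six mediators carries the larger part of the stress effect. Any path from stress through craving to drinking that does not pass through an analysed mediator is counted in the direct effect. If the five analysed mediators explain less than half, H4 is not refuted, because the contribution of craving is missing. If they explain more than half, the role of craving is still untested.

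**Emotional distress.** The mediation paragraph reserves a place for self-reported stress, but no instrument in the Mediators block measures it. The only row in Table 1 that names a stress self-report is the Perceived Stress Scale. It measures current stress load, sits in the confounder block and belongs to the baseline package in the text above the table. The construct probably has an analysis, but the article does not say which measure feeds it.

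**Timing.** The readable text does not say when the ACQ-R, the mood questionnaire or the STAI affect measure is given. Craving and mood state are not in the Procedure section's list of baseline questionnaires, and no post-stress rating is described. Fig. 5 is not shown. Either answer leaves a conflict:

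- If craving is rated after the stress or placebo task, the confounder label is wrong for that rating and the analysis is missing.
- If craving is rated only at baseline, it may serve as a covariate but cannot mediate, and H4 claims too much.

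**The case against.** The strongest reply is that little follows beyond a mismatch of lists. Three parts of it stand.

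- **Over-adjustment is not planned.** A reader might infer from the Table 1 heading that post-stress craving or mood will enter the models and absorb part of the effect. No sentence says so. The covariate examples are age, time of day, beer preference, previous stressful events and previous alcohol use. None of these is a response to the stressor. In a counterfactual mediation framework a factor common to mediator and outcome means a common cause, not a consequence of exposure. The wording is open-ended, so a risk remains, but only if these variables are rated after the stressor and are then chosen as covariates.
- **The main stress effect is not touched.** A reader might infer that the total effect would shrink. The main regression adjusts for soft-drink intake and, where groups differ by chance, for baseline characteristics associated with drinking. A post-stress rating is not a baseline characteristic. The risk is confined to the mediation models.
- **Emotional distress is not without an analysis.** Self-reported stress is a plausible stand-in, and an article may leave the choice of instrument to the full protocol. This limb is a labelling gap.

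The reply does not remove the conflict over craving. That is a contradiction between statements in the article, not detail left to another document.

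**Conclusion.** The point holds for craving. One of the six H4 mediators, and one of the two that separate H4 from H3, is labelled a confounder in Table 1 and has no mediation analysis. This rests only on the text of the three sections and needs no assumption about when craving is measured.

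It would go too far to say that H4 cannot be tested at all. Five components can be analysed, with emotional distress depending on what self-reported stress turns out to be. What cannot be done is to test H4 as worded.

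The size of any bias from adjusting for post-stress craving or mood cannot be derived. The article gives neither the paths involved nor the timing of the ratings, and it does not state such an adjustment.

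**What to change.** Reconcile the three lists before analysis:

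1. State when the ACQ-R, the mood questionnaire and the STAI affect measure are given, relative to the stress or placebo task and the taste test.
2. If craving is rated after the task and before the taste test, move it to the Mediators block of Table 1 and add it to the mediation list under Statistical analyses. Allow only a pre-stress craving rating as a covariate.
3. If craving is rated only at baseline, remove it from H4 and say so.
4. Name the instrument that serves as the emotional-distress or self-reported-stress mediator, and list it in the Mediators block.
5. Limit the confounders in the mediation models to variables measured before the stress or placebo task.

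The cost is a reclassification in Table 1, a line or two under Statistical analyses and a statement of timing. If a post-stress craving rating exists, no new procedure is needed. If it does not, H4 is narrowed. The article reports 213 complete data sets to March 2022 against a target of 400 (213/400 = 53%), with collection continuing, so at that point the change could still be made before the final analysis.

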### Study progress and preliminary feasibility data

The data collection of the presented MESA study started in December 2018. From December 2018 until March 2022 N = 623 persons participated in the online screening. A total of 213 complete data sets have been collected so far. All participants are male and between 18–40 (*M* = 25) years old. 97 of the 213 participants took part in the stress condition, stratified in 40 risky drinkers and 57 regular drinkers. Further, 117 participants took part in the control condition stratified in 36 risky drinkers and 81 regular drinkers. More than half reported they were university students.

Due to the Covid-19 pandemic, the study was paused in the beginning of March 2020 in order to protect the safety and health of all personnel involved in the study and to comply with legislative regulations. The laboratories reopened in September 2021 and data collection was continued.

## Discussion

The present MESA study was developed in response to the incomplete understanding of the underlying mechanisms of the relationship between stress and alcohol consumption. As pointed out, there is a significant amount of people suffering from AUDs with tremendous consequences for the individual as well as for society and health care systems. There is need for preventive interventions at the biological, psychological or social level for individuals at high risk of problematic alcohol consumption before the manifestation of AUD. Research to date has focused primarily on secondary prevention, which aims to prevent AUD progression and relapse, and tertiary prevention, which aims to minimize functional deterioration in chronic AUDs [117]. The present study focuses on the identification of targets for primary prevention, which is focused on the protection of healthy individuals, and may be provided on a universal, selective or indicated level. The various tasks designed to examine different, potential moderators and mediators can then be used to develop interventions and provide information for the at-risk population. The identification of specific mediators is of key importance as they help to elucidate what mechanisms underlie the association between stress and alcohol consumption. Knowledge about specific mechanisms are of high relevance as it can be used to allocate existing interventions. For example, there are already trainings for many of the investigated mediators (e.g. Attentional Bias Modification, Inhibitory Control trainings), which, should these factors prove to be relevant, could then be specifically adapted and applied in the context of stress [118, 119, 120, 121]. It can also be used to develop novel interventions that might be useful to prevent stress-related alcohol consumption. Identifying specific moderators will help to tailor these preventive interventions to at high-risk individuals, which increases their potential efficacy and cost-effectiveness.

Given its focus on internal validity using a carefully controlled design in a laboratory setting, external validity will be a limitation of this study. Thus, findings will have to be complemented by investigations in real world settings to make definite conclusions about the association between stress and alcohol use and its underlying mechanisms. This could be achieved for example with ecological momentary assessments, which have shown good feasibility in a couple of promising recent studies on stress-related alcohol use and the role of craving, alterations in mood and inhibitory control [122, 123, 124, 125].

Taken together, the presented study has a high potential to advance our understanding of stress-related alcohol use. In the long-term, it could stimulate the development of tailored preventive interventions and contribute to a reduction of problematic alcohol use.

## Data Availability

The data will be made available on the OSF after completion of the first data analyses.

## Abbreviations

AUC: Area under the curve
AUC_G_: Area under the curve with respect to ground
AUC_I_: Area under the curve with respect to increase
AUD: Alcohol use disorder
BIS: Balanced integration score
DERS: Difficulties in emotion regulation scale
DMQ-R: Drinking Motive questionnaire—revised
HPA-axis: Hypothalamic–pituitary–adrenal axis
MBDF: Multidimensional Mood State Questionnaire
MESA: Underlying mechanisms in the relationship between stress and alcohol consumption in regular and risky drinkers
PCs: Proportion of correct responses
PSS: Perceived Stress Scale
RTs: Response times
SNS: Sympathetic nervous system
STAI: State-trait-anxiety-inventory
TSST: Trier Social Stress Test
